### Patient eligibility

Data is being abstracted for patients who: (a) have at least one of the ABCS risk factors (i.e., eligible for aspirin, has a diagnosis of hypertension, meets criteria for blood cholesterol management, and/or is a current smoker); (b) have received care at the site in the last 12 months; and (c) are age >18 years. Patients eligible for aspirin are those with a documented ICD (ICD-9/10) code for ischemic vascular disease in the last 12 months. Similarly, patients with a diagnosis of hypertension must have a documented ICD code for the targeted risk factor. Patients with hyperlipidemia based on an ICD code or who otherwise meet criteria for cholesterol management are identified by laboratory results for LDL cholesterol as well as ICD codes. Smokers are identified by documentation of current smoking status in the EHR (e.g., meaningful use measure) during the past 24 months.

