#### Practice facilitator training and supervision

All practice facilitators received training at the State University of New York at Buffalo Practice Facilitator Certificate Program, a 92-h course with 13 weekly 1.5-h live online classes plus a 40-h fieldwork practicum and 26 h of reflective learning [34]. Twenty-one modules, based on AHRQ’s Practice Facilitation Handbook, cover the full range of topics for trainees to achieve the four core competencies for practice facilitation: data use to drive improvement; interpersonal skills; Health IT optimization; and QI and change management methods (e.g., Plan-Do-Study-Act) [35]. PCIP supplemented the Buffalo program with an additional 20 h of training that focused on increasing knowledge of the ABCS practice guidelines and optimizing the use of the EHR, including creating registries and dashboards, activating clinical decision support systems and other practice change components that correspond to the PF activities in the PCIP QI manual. ABCS toolkits were developed for the practice facilitators to follow that correspond directly to the training content. Three PF managers meet weekly with up to five facilitators each to provide oversight and opportunities for problem solving, identify additional training needs or site specific resources, and review the structured weekly activity reports and monthly narrative reports.

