#### Outcome measures and data source

The primary outcome is the proportion of patients who reach clinical goals for hypertension, blood cholesterol management, aspirin use, and smoking cessation assistance (Table 2). The measures were defined by AHRQ EvidenceNOW and finalized through a collaborative process across all the seven funded groups. We will collect data for the 12-month period prior to implementing the intervention, during the 12-month intervention period, and then 6 months post-intervention. These data will be extracted from the EHRs of all 250 participating sites using PCIP’s Hub, a query architecture that enables execution of queries in independent EHRs of the participating practices with data subsequently transmitted to a secure centralized clinical data repository [28]. The Hub provides a platform for HHNYC to extract numerator and denominator data for the ABCS measures. The underlying data quality/integrity of practices connected to the Hub is based on assessment of documentation patterns at the practices (e.g., completeness of use of routine structured data fields such as demographics, diagnosis, vital signs, and smoking status) as well as utilization of electronic laboratory interfaces, to ensure laboratory results data are available in electronic format [36].

**Table 2 Tab2:** Outcome measures, data source, and data collection timeline

Domain	Measures	Data source	Administration

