Primary outcomes	• Aspirin: percent of patients aged 18 years and older with ischemic vascular disease (IVD) with documented use of aspirin or other antithrombotic. • Blood pressure management: 1) Percent of patients aged 18–85 who had a diagnosis of hypertension (HTN) and whose blood pressure (BP) was adequately controlled (<140/90). 2) Percent of patients aged 60–85 without diabetes (DM) or chronic kidney disease (CKD) with controlled BP (<150/90), 3) Percent aged 18–85 with DM or CKD with controlled BP (<140/90) • Cholesterol management: 1) Percentage of patients aged >21 diagnosed with ASCVD who are on statin therapy. 2) Percentage of patients aged >21 with history of LDL >190 mg/dL without ASCVD who are on statin therapy. 3) Percentage of patients aged 40–75 with diabetes without ASCVD and LDL 70–189 mg/dL who are on statin therapy • Smoking cessation support: Percentage of patients aged 18 years or older who were screened about tobacco use one or more times within 24 months and who received cessation counseling intervention if identified as a tobacco user.	EHR	Baseline, quarterly during intervention period, at the end of intervention (12 months), and 6 months post intervention
Secondary outcome: practice change capacity	• Organizational change process capacity • Adaptive reserve	Provider and staff survey	Baseline, at the end of intervention (12 months) and 6 months post intervention

The secondary outcome is changes in primary care practice capacity captured through the use of the change process capacity questionnaire and the 23-item adaptive reserve scale [31, 32]. These measures will be obtained through provider and staff surveys at three time points: baseline, immediately following the 12-month intervention and 6 months post-intervention.

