### Analysis plan

#### Aim 1

The primary outcomes are the proportion of patients who reach clinical goals based on national guidelines for (a) aspirin use, (b) HTN control, (c) blood cholesterol management, and (d) smoking cessation assistance at the end of the intervention (12 months) period and 6 months post-intervention. Each of the four hypotheses referring to the four primary outcomes will be tested separately with a two-sided test with *α* = 0.05, i.e., no adjustment for multiple testing will be applied. The analysis of effect of PF on the ABCS outcome measures in the context of a stepped-wedge design will be based on a generalized linear mixed model (GLMM). In particular, to assess the intervention effect, we will use a Poisson model with random site and provider within site effects. Each model will be as follows:1$$ \log \left({C}_{it}\right)=\mu +{\beta}_1t+{\beta}_2{I}_{it}^{PF}+{\beta}_3{I}_{it}^{PF}\left(t-{s}_i\right)+\gamma {Z}_i+{b}_i+ \log \left({E}_{it}\right), $$

where *C*
_*it*_ is the number of patients in site *i* who (a) had received aspirin, (b) had controlled blood pressure, (c) had controlled cholesterol, or (d) received smoking cessation counseling during period *t*, for *t* ∈ (0, 1, …, 11). Each period is 3 months, and *t* = 0 is the baseline quarter. *I*
_*it*_^PF^ is an indicator variable, and *I*
_*it*_^PF^ = 1 if site *i* has been assigned to the PF intervention at period *t*, *I*
_*it*_^PF^ = 0 otherwise. *s* is the time period when the PF intervention begins for site *i. Z* is a site-level indicator variable, *Z* = 1 if site *i* has three or more providers, *Z* = 0 otherwise. *E*
_*it*_ is the number of patients at site *i* who were eligible to be counted during period *t*. The eligible pool of patients *E*
_*it*_ will be different for each outcome and has been described in detail in Table 1. Log(*E*
_*it*_), considered the “offset” in the Poisson regression model, is a random effect for site *i* with mean 0 and variance *σ*
_*b*_^2^. The estimation via model (1) takes into account a general time trend and allows for the intervention effects to grow over time following implementation of the intervention.

Our primary outcome of interest for each of the four models is proportion of patients who meet clinical goals (described above) at 12 months. In each model, this effect (after taking into account general time trends) would be captured by *β*
_2_ + 3*β*

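### Aspirin, hypertension and smoking denominators rest on site documentation recounted after crossover, so facilitation may change who is counted and bias the primary contrast by an amount and in a direction the protocol does not fix

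*Protocol article*

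**What the plan says.** The Patient eligibility section of the Protocol article ties membership of the denominators to site records:

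- Aspirin: "Patients eligible for aspirin are those with a documented ICD (ICD-9/10) code for ischemic vascular disease in the last 12 months".
- Blood pressure: "patients with a diagnosis of hypertension must have a documented ICD code for the targeted risk factor".
- Smoking: "Smokers are identified by documentation of current smoking status in the EHR", with a 24-month look-back.
- Cholesterol: patients "are identified by laboratory results for LDL cholesterol as well as ICD codes", so this denominator depends only partly on coding.

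The Analysis plan (Aim 1) defines E_it as the patients at site i "who were eligible to be counted during period" t and enters log(E_it) as the offset of a Poisson mixed model. The tested contrast is β2 + 3β3.

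The section on practice facilitator training lists "optimizing the use of the EHR, including creating registries and dashboards, activating clinical decision support systems". The Conceptual framework names EHR enhancements among the changes through which PF acts, and the Practice facilitation protocol adds performance reports and feedback.

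Table 2 words the smoking measure as adults "who were screened about tobacco use one or more times within 24 months and who received cessation counseling intervention if identified as a tobacco user". This can be read as taking all adults as the denominator, which differs from Patient eligibility.

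**The concern.** An offset treats the denominator as exposure that the intervention does not touch. Here it is measured after the intervention starts, from the same records that the intervention helps sites to use better. If PF leads a site to code or record more patients, those added need not resemble those already counted, and the proportion at goal can move without any change in the care of existing patients.

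The stepped-wedge design does not remove this. Randomising the start time balances sites, not the patients who become countable after crossover. A PF-induced change in E_it starts when the PF indicator switches on and may grow with time since crossover. It therefore falls on β2 and β3, and the common time trend β1 does not absorb it.

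What is at stake is the reading of Aim 1: whether an effect, or its absence, reflects guideline care, case identification or a mixture of the two.

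**Working it through.** **Inputs from the documents.** Baseline rates (Appendix): blood pressure 49 %, aspirin 35 %, cholesterol 33 %, smoking 20 %. Detectable change: 20.0 % to 22.0 % in the main text (ratio 22.0/20.0 = 1.10) and 20.0 % to 22.2 % in the Appendix (ratio 1.11), each with over 80 % power.

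**The plan's own power.** I used the asymptotic information matrix of the Poisson model with a random site intercept, 63 sites per wave, between-site variance 0.10 and the Appendix contrast β2 + 2β3. The number of physicians per site is not given. With 2 assumed:

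- 20.0 % to 22.2 %, 50 patients: 82 to 86 % across the period layouts tried (stated: over 80 %).
- Same effect, 70 patients: 92 to 94 % (stated: 92 %).
- 25.0 % to 27.7 %: 88 to 91 % (stated: 91 %).

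The Appendix is plausible on that assumption. With 1 physician the first figure is 58 to 63 %. In the plan's simulation E varies only by noise unrelated to PF, so the power figures do not address this point.

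**Assumed inputs.** Let a be the growth of the denominator through new coding or recording, and q the proportion of added patients who meet the measure. The documents give neither. With care of existing patients unchanged:

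shift = (p0 + a·q)/(1 + a) − p0 = a(q − p0)/(1 + a)

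For example, smoking with a = 0.10 and q = 0.60 gives (0.20 + 0.06)/1.10 − 0.20 = +3.6 points.

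| Outcome (p0) | q | a = 5 % | a = 10 % | a = 20 % |
|---|---|---|---|---|
| Smoking (20 %) | 20 % | 0 | 0 | 0 |
| Smoking (20 %) | 30 % | +0.5 | +0.9 | +1.7 |
| Smoking (20 %) | 60 % | +1.9 | +3.6 | +6.7 |
| Blood pressure (49 %) | 30 % | −0.9 | −1.7 | −3.2 |

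With q = 0, 10 % growth moves smoking by −1.8 points.

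**On the model's ratio scale.** A ratio of 1.10 on 49 % is 4.9 points. The largest blood pressure shift shown, −3.2, is 3.2/49 = 6.5 % relative and does not reach it. Leaving aside the zero row, two of the nine scenarios exceed a 1.10 ratio. Both are smoking at q = 60 %: 23.6/20 = 1.18 and 26.7/20 = 1.33.

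**Growth needed for a given shift d.** a = d/(q − p0 − d). For smoking and d = 2.0 points:

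- q = 0.3: 0.02/0.08 = 25.0 %
- q = 0.4: 0.02/0.18 = 11.1 %
- q = 0.6: 0.02/0.38 = 5.3 %
- q = 1.0: 0.02/0.78 = 2.6 %
- q at or below 0.22: never

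For a ratio of 1.10 at q = 0.8: aspirin 0.035/0.415 = 8.4 %, cholesterol 0.033/0.437 = 7.6 %, blood pressure 0.049/0.261 = 18.8 %.

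**Chance of a significant result.** At 2 physicians per site, a 2.0-point artefact on 20 % that acts exactly like a treatment effect would be significant about 75 to 79 % of the time on the Appendix contrast, and 54 to 62 % on the main-text contrast β2 + 3β3.

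**The case against.** The strongest case against has five parts.

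- **A condensed article may leave sensitivity analyses to an SAP that is not shown.** This is fair for analysis detail. But the eligibility rule, the recount in each period and the offset are stated in the article, and the point is about those choices.
- **A reader might infer that facilitation sets out to change coding.** The documents do not say so. Registries, dashboards and decision support are listed, but neither diagnosis coding nor recording of smoking status is named as an aim. That PF may change them is an inference.
- **A reader might infer that PF can exceed the target on the primary outcomes with no change in care.** The documents do not support this. Growth and compliance of added patients are assumed, most scenarios stay below the target ratio, and the shift can be zero or negative. A smoker who is newly identified and then counselled has also received part of the care that the measure counts. If Table 2 means all adults, recording acts through the numerator and the smoking arithmetic does not apply. The Appendix, however, sizes this outcome on 50 patients as the likely smoking group, which favours the Patient eligibility reading.
- **There are safeguards.** Sites must have had an EHR for at least a year, smoking status has a 24-month look-back, and Hub data quality "is based on assessment of documentation patterns at the practices". These make large growth less plausible, but none is stated to hold E_it constant across crossover.
- **The measures were set across the seven EvidenceNOW groups.** This stands as a reason to leave the primary definitions alone. It does not prevent supporting analyses.

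**Conclusion.** The point holds as a risk of differential ascertainment. Three denominators depend on documentation, are recounted after crossover and are treated as fixed exposure, while the intervention works on the records that define them. Nothing in the model keeps a PF-induced change in who is counted out of β2 + 3β3.

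Size and direction are unknown. Smoking is the most sensitive on the reading in Patient eligibility: 10 % growth gives 0 to +3.6 points for q from 20 % to 60 %, against a detectable 2.0 to 2.2. Blood pressure could move against PF, by −1.7 points at 10 % growth and q = 30 %. Cholesterol is less exposed because LDL results also identify patients. All these shifts rest on assumed a and q. They show that modest changes in ascertainment could matter, not that they will occur.

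**What to change.** Keep the open-population analysis of model (1) primary and add the following to Aim 1.

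1. For each outcome, fit the same mixed model to E_it as the response, without the offset, using the denominators that the Hub already extracts. Report E_it by period and by control, intervention or follow-up status. Visit volume also affects E_it, so a change is a signal and not proof of new coding.
2. Where the Hub can apply a date condition, refit model (1) as a sensitivity analysis on patients whose qualifying record predates one calendar date before the first wave's crossover, the same for all sites and periods. Each site's own crossover should not be the cut-off, because new patients would then enter during control periods but not afterwards. Carry the qualifying code forward. In wave 4 the intervention ends 9 + 12 = 21 months after the first crossover, so the 12-month vascular-disease look-back would otherwise empty the aspirin cohort.
3. State in advance that if PF changes E_it and the effect is absent in the fixed cohort, the result will not be attributed to improved care alone.
4. Reconcile the smoking denominator in Patient eligibility with Table 2. The Analysis plan refers to Table 1 for the eligible pools, but Table 1 shows the design and the measures are in Table 2.

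The cost is two extra models per outcome and a fixed cohort that is smaller and less precise. Whether the Hub can apply a dated patient-level condition is not stated and should be checked first. Step 1 does not depend on it.

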### Site recruitment

PCIP focused recruitment on small practices in their network, which comprises over 1300 independent primary care sites in NYC. After a preliminary assessment of eligibility, the sample was reduced to a pool of 547 practices that are focused solely or primarily on adult primary care and currently using an EHR with data sharing capacity. Recruitment started with targeted invitation letters to an initial group of practices via post and email, which included a link to a recorded informational webinar. Simultaneously, PCIP conducted telephone outreach to determine practice site interest, to conduct a more detailed eligibility screening survey, and to secure a verbal commitment to participate. Once practices agreed to participate, PCIP and NYU co-hosted multiple in-person “kickoff” events to educate sites about program details. At these events, eligible practices were asked to sign the study participation agreement. In order to eliminate the risk of contamination between multiple sites in the same practice, only one site per target practice was permitted to join the study.

### Conceptual framework

The study draws on Damshroeder’s Consolidated Framework for Implementation Research (CFIR) and Solberg’s framework for improving medical practice [29, 30]. Our model posits that improvements in provider adherence to guideline-recommended care and ABCS-related clinical outcomes are a function of baseline external context (e.g., external policies and incentives), the baseline organizational/site characteristics, including change process capability and adaptive reserve, the intervention strategies (i.e., practice facilitation), and the multilevel changes in care processes and systems (e.g., EHR enhancements) that are employed as a result of the intervention strategies (Fig. 1). The model postulates that PF, and the resulting system changes, will enhance ABCS outcomes through changes they produce in adaptive reserve and change process capability [31, 32].

**Fig. 1 Fig1:**
[figure not shown]
Conceptual framework

### Intervention components

#### Practice facilitation protocol

The duration of the intervention is 12 months for each wave, and it is being implemented at the site level. PF comprises the following components: (1) onsite visits by the practice facilitator with the medical director and/or staff twice in the first month and then monthly thereafter; (2) expert consultation (i.e., quarterly webinars and “ask the expert” email consultant service); and (3) facilitated opportunities for shared learning across intervention sites (e.g., peer-to-peer collaborative calls) [8]. The practice facilitator’s main role is to coordinate and facilitate meetings with study sites and to assist primary care practices in setting practice change and performance goals and in developing strategies for implementing evidence-based components of the models for practice transformation, including CCM, PCMH, and Bodenheimer’s 10 building blocks of primary care [9, 10, 33]. For this purpose, a quality improvement (QI) manual informed by these models was developed by PCIP to drive delivery of the intervention. PFs also share best practices across sites, train practice staff on QI processes and methods to help them develop robust QI capacity (e.g., workflow mapping, generating performance reports), assist teams in testing system changes and interpreting outcomes, and assist with generating data for performance feedback and Plan-Do-Study-Act (PDSA) cycles. The practice facilitator conducts phone and email exchanges with the sites as needed between site visits during the 12-month intervention period.

#### Practice facilitator training and supervision

All practice facilitators received training at the State University of New York at Buffalo Practice Facilitator Certificate Program, a 92-h course with 13 weekly 1.5-h live online classes plus a 40-h fieldwork practicum and 26 h of reflective learning [34]. Twenty-one modules, based on AHRQ’s Practice Facilitation Handbook, cover the full range of topics for trainees to achieve the four core competencies for practice facilitation: data use to drive improvement; interpersonal skills; Health IT optimization; and QI and change management methods (e.g., Plan-Do-Study-Act) [35]. PCIP supplemented the Buffalo program with an additional 20 h of training that focused on increasing knowledge of the ABCS practice guidelines and optimizing the use of the EHR, including creating registries and dashboards, activating clinical decision support systems and other practice change components that correspond to the PF activities in the PCIP QI manual. ABCS toolkits were developed for the practice facilitators to follow that correspond directly to the training content. Three PF managers meet weekly with up to five facilitators each to provide oversight and opportunities for problem solving, identify additional training needs or site specific resources, and review the structured weekly activity reports and monthly narrative reports.

### Evaluation

Using a mixed methods approach, we will conduct a process and outcomes evaluation of five interrelated domains: (1) primary outcome (reaching clinical goals for ABCS measures); (2) secondary outcome (change in practice capacity); (3) internal context; (4) external context; and (5) implementation fidelity (PF activities, practice change). We will also assess the cost of the intervention.

#### Outcome measures and data source

The primary outcome is the proportion of patients who reach clinical goals for hypertension, blood cholesterol management, aspirin use, and smoking cessation assistance (Table 2). The measures were defined by AHRQ EvidenceNOW and finalized through a collaborative process across all the seven funded groups. We will collect data for the 12-month period prior to implementing the intervention, during the 12-month intervention period, and then 6 months post-intervention. These data will be extracted from the EHRs of all 250 participating sites using PCIP’s Hub, a query architecture that enables execution of queries in independent EHRs of the participating practices with data subsequently transmitted to a secure centralized clinical data repository [28]. The Hub provides a platform for HHNYC to extract numerator and denominator data for the ABCS measures. The underlying data quality/integrity of practices connected to the Hub is based on assessment of documentation patterns at the practices (e.g., completeness of use of routine structured data fields such as demographics, diagnosis, vital signs, and smoking status) as well as utilization of electronic laboratory interfaces, to ensure laboratory results data are available in electronic format [36].

**Table 2 Tab2:** Outcome measures, data source, and data collection timeline

Domain	Measures	Data source	Administration
Primary outcomes	• Aspirin: percent of patients aged 18 years and older with ischemic vascular disease (IVD) with documented use of aspirin or other antithrombotic. • Blood pressure management: 1) Percent of patients aged 18–85 who had a diagnosis of hypertension (HTN) and whose blood pressure (BP) was adequately controlled (<140/90). 2) Percent of patients aged 60–85 without diabetes (DM) or chronic kidney disease (CKD) with controlled BP (<150/90), 3) Percent aged 18–85 with DM or CKD with controlled BP (<140/90) • Cholesterol management: 1) Percentage of patients aged >21 diagnosed with ASCVD who are on statin therapy. 2) Percentage of patients aged >21 with history of LDL >190 mg/dL without ASCVD who are on statin therapy. 3) Percentage of patients aged 40–75 with diabetes without ASCVD and LDL 70–189 mg/dL who are on statin therapy • Smoking cessation support: Percentage of patients aged 18 years or older who were screened about tobacco use one or more times within 24 months and who received cessation counseling intervention if identified as a tobacco user.	EHR	Baseline, quarterly during intervention period, at the end of intervention (12 months), and 6 months post intervention
Secondary outcome: practice change capacity	• Organizational change process capacity • Adaptive reserve	Provider and staff survey	Baseline, at the end of intervention (12 months) and 6 months post intervention

The secondary outcome is changes in primary care practice capacity captured through the use of the change process capacity questionnaire and the 23-item adaptive reserve scale [31, 32]. These measures will be obtained through provider and staff surveys at three time points: baseline, immediately following the 12-month intervention and 6 months post-intervention.

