**Discussion:**

We hypothesize that practice facilitation will result in superior clinical outcomes compared to usual care; that the effects of practice facilitation will be mediated by greater adoption of system changes in accord with PCMH and CCM; and that there will be increased adaptive reserve and change capacity.

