### Study design

HHNYC is a stepped-wedge cluster randomized controlled trial that is designed to evaluate the implementation process and the impact of PF (intervention) compared to usual practice (control), on implementation of the Million Hearts ABCS treatment guidelines in 250 primary care practices. All practice sites begin as part of the control condition and are block-randomized into four waves with each wave beginning 3 months after the start of the prior wave and lasting for 12 months (see Table 1). All clusters eventually receive the intervention, and outcomes will be measured every 3 months in all clusters. We anticipate, conservatively, a 15 % attrition rate; therefore, we have enrolled 290 sites to ensure that enrollment of the required 250 sites is achieved at the end of the study. This study has received Institutional Review Board approval by the New York University School of Medicine.

**Table 1 Tab1:** Stepped-wedge study design

	Year 1 (months)				Year 2 (months)				Year 3 (months)			
Clusters	3	6	9	12	15	18	21	24	27	30	33	36
	Time period											
1 (80 sites)		C	X	X	X	X	F	F				
2 (70 sites)		C	C	X	X	X	X	F	F			
3 (70 sites)		C	C	C	X	X	X	X	F	F		
4 (70 sites)		C	C	C	C	X	X	X	X	F	F	

*C* control period, *X* intervention period, *F* follow up period

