We will identify baseline organizational characteristics (e.g., site level adaptive reserve, organizational change capacity) that are associated with primary outcomes. This will be accomplished by including separately each organizational characteristic in the main models used under Aim 1 as a main effect and in interactions with the PF indicator. We will conduct a further analysis to explore the possibility that changes in organizational level factors mediate the effect of the intervention on the primary compliance outcomes. Mediation analysis methods in the context of a stepped-wedge design have not been well developed. We will conduct a preliminary analysis to assess if the intervention is associated with changes in site level adaptive reserve, organizational change capacity, and practice changes (assessed with the practice change survey). If there is a detectable effect of the intervention on the organizational level factors, we will assess whether the changes in these organizational level factors are associated with changes in the primary compliance outcomes using the Baron and Kenny “product method” as a starting point of the analysis [38]. If necessary, we will explore more complex structural equation models (SEM) adapted for Poisson outcomes as well as more recently developed causal inference mediation methods to evaluate the mediation.

#### Aim 3

We will use qualitative methods to conduct a more in-depth assessment of internal and external context including barriers and facilitators (among high and low performers) to implementing practice change and achieving ABCS outcomes. The transcriptions of the interviews and focus groups will be coded using Atlas.ti. The coding scheme will be developed by the evaluation team to focus on key dimensions identified both a priori (i.e., from the interview and focus group protocols) and those that emerge during site visits, interviews, and focus groups. Two coders will independently code at least 10 interviews and all focus groups. Double coding will continue until adequate inter-rater reliability is achieved.

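### No survey of the secondary outcome after facilitation has a concurrent usual-care survey, so a facilitation effect on it can be separated from secular change only by an assumed, extrapolated time trend

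*Protocol article*

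**What the plan says.** The Study design section says that sites are "block-randomized into four waves with each wave beginning 3 months after the start of the prior wave and lasting for 12 months", and that "outcomes will be measured every 3 months in all clusters". The second statement does not describe the secondary outcome. Under Outcome measures and data source, the text obtains that outcome through "provider and staff surveys at three time points: baseline, immediately following the 12-month intervention and 6 months post-intervention", and Table 2 gives the same schedule: "Baseline, at the end of intervention (12 months) and 6 months post intervention".

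The abstract hypothesises that "there will be increased adaptive reserve and change capacity". Aim 2 of the analysis plan then says: "We will conduct a preliminary analysis to assess if the intervention is associated with changes in site level adaptive reserve, organizational change capacity". If an effect of the intervention on these factors is detected, the mediation analysis follows.

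The Discussion lists practice transformation programmes running at the same time (Medicaid PCMH incentives, meaningful use, DSRIP). It says that key informant interviews together with provider surveys before and after the intervention will allow historical threats to validity to be analysed. The general time trend under Aim 1 belongs to model (1), the Poisson model for the ABCS counts. No model is given for the survey outcome.

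**The concern.** A stepped-wedge trial guards against secular change because, at a given calendar time, some clusters are still in usual care while others have crossed over. The quarterly ABCS data have such times. The survey is tied to each site's own start and end of facilitation, and its post-facilitation occasions all seem to fall after the last control period.

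If so, a rise in capacity caused by the concurrent programmes could look like a result of facilitation. It could also meet the condition for going on to mediation, and so support a causal account of how facilitation works. Data collection timing is fixed in the article, and no later analysis plan can supply control surveys that were never scheduled.

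**Working it through.** The article states no power or effect size for the secondary outcome, so there is no figure to reproduce. The check places the three surveys on the Table 1 calendar.

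**Inputs.** Table 1 column headings are read as the month in which each quarter ends. Another convention would shift every wave equally and change nothing below.

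| Wave (sites) | Last control month | End of 12-month facilitation | 6 months later |
|---|---|---|---|
| 1 (80) | 6 | 18 | 24 |
| 2 (70) | 9 | 21 | 27 |
| 3 (70) | 12 | 24 | 30 |
| 4 (70) | 15 | 27 | 33 |

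**Overlap.** The latest possible usual-care survey is at month 15 and the earliest end-of-intervention survey is at month 18. The number of control sites is 0 at all 4 × 2 = 8 post-facilitation surveys. This holds whether baseline is a common survey at month 6 or is taken just before each wave starts (months 6, 9, 12, 15). Table 1 has control and intervention sites together only at months 9, 12 and 15.

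**Size of the confounding.** Let the outcome drift by d per quarter for reasons unrelated to facilitation.
- Wave-specific baseline: the gap to the 12-month survey is (18 − 6)/3 = 4 quarters in every wave, so the drift adds 4d.
- Common baseline at month 6: the gaps are 4, 5, 6 and 7 quarters. The site-weighted mean is (80×4 + 70×5 + 70×6 + 70×7)/290 = 1580/290 = 5.4, so the drift adds 5.4d on average.

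**Can a model remove it?** The rank of the design matrix was examined with separate 12-month and 18-month effects.
- *Unrestricted (categorical) calendar time.* Every survey month is either wholly before or wholly after facilitation, so the indicators for the later months add up to the indicator for having been facilitated. The 12-month effect is not identified under either reading of baseline, with or without wave effects.
- *Linear time, wave-specific baselines, within-site comparison.* In quarters, calendar time = (wave's baseline time) + 4 × (12-month survey) + 6 × (18-month survey). Time is an exact combination of the other columns (rank 6 of 7), so the effect is not identified.
- *Linear time, wave-specific baselines, no wave effects.* Identified from the staggered baselines of randomised waves. Its variance is 0.02124/0.00690 = 3.1 times that of the unadjusted before-after estimate.
- *Linear time, common baseline.* Identified from the unequal gaps. The variance ratio is 0.04682/0.00690 = 6.8 without wave effects and 0.12668/0.00690 = 18 with them.

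The ratios assume independent errors and the site numbers in Table 1. Each identified case relies on the trend staying linear beyond the last control survey.

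**The case against.** A reader might infer that change under usual care is never observed and that any secular change must be credited to facilitation. The documents do not support that. If baseline is taken just before each wave starts, randomised waves are surveyed under usual care at months 6, 9, 12 and 15. Differences between those baselines estimate nine months of usual-care change without two surveys at any one site. A linear trend could then be estimated and carried forward. The article also states no analysis model for the survey, so it cannot be said to plan a raw before-after comparison.

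The wording is also restrained. The explicit comparison with usual care is attached to the ABCS outcomes. For capacity, the article expects an increase, and Aim 2 calls its first step preliminary and admits that mediation methods for this design are not well developed.

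Nor is the contrast with the primary outcomes absolute. Their 12-month effect also falls at months 18 to 27, when no site is in control, and leans on a modelled trend. Quarterly data with controls and intervention sites together at months 9, 12 and 15 support that trend far better, but the difference is one of degree.

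What remains is that no post-facilitation survey has a concurrent control, under any reading. Aim 2 does make a detected effect of the intervention the condition for mediation. And the safeguard in the Discussion supplies no control data: surveys before and after facilitation cannot by themselves separate it from the programmes listed there. The practice change survey does not help either, because facilitators complete it after their visits.

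**Conclusion.** The point holds in this form. The survey schedule gives no concurrent usual-care comparison for the secondary outcome: 0 control sites at all eight post-facilitation surveys. An effect of facilitation on it, and so the first step of the mediation analysis, depends on a parametric calendar trend extrapolated past month 15. The article states no such analysis, and its assurance about historical threats does not hold for this outcome. Without adjustment, the confounding is 4d at 12 months with wave-specific baselines, and 4d to 7d by wave with a common one. The documents give no value for d.

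The conclusion rests on Table 1 and on the three survey times that the text and Table 2 both give. It should be put right, but it concerns a secondary outcome and an exploratory mediation step. It does not touch the primary ABCS analysis.

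**What to change.** Choose one of two.

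(a) Take baseline in all waves at the same calendar time, in the first control quarter (month 6), and add one survey of waves 1 and 4 at month 15. Estimate the effect as the change in wave 1 minus the change in wave 4, both over months 6 to 15. State that this is the effect in the third quarter of facilitation, because no control site remains at month 18. Setting wave 1 over months 6 to 18 against wave 4 over months 6 to 15 would not do, since it leaves three months of secular change in the estimate. The cost is one extra round at about 80 + 70 = 150 sites, with respondent burden and incentive payments. The article already names survey response as a challenge.

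(b) Keep the schedule. Label the secondary result and the first mediation step an uncontrolled before-after change, or a change adjusted for an assumed linear trend with that assumption stated. Do not describe it as an effect of the intervention, and correct the Discussion's assurance about historical threats. This needs no extra data; the price is a weaker claim.

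Under either option, limit the Study design statement on three-monthly measurement to the EHR outcomes.
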